## Acronyms

|         |   |                                         |
|---------|---|-----------------------------------------|
| SAM     | - | Severe Acute Malnutrition               |
| CHAI    | - | Clinton Health Access Initiative        |
| KSMOH   | - | Kano State Ministry of Health           |
| SMC     | - | Seasonal Malaria Chemoprevention        |
| WHO     | - | World Health Organization               |
| SP - AQ | - | Sulfadoxine-pyrimethamine + Amodiaquine |
| KSMCP   | - | Kano State Malaria Control Program      |
| LNS     | - | Lipid-based Nutritional Supplement      |
| Q-1     | - | Question 1                              |
| Q-2     | - | Question 2                              |
| Q-3     | - | Question 3                              |
| H-1     | - | Hypothesis 1                            |
| H-2     | - | Hypothesis 2                            |
| H-3     | - | Hypothesis 3                            |
| LGA     | - | Local Government Area                   |
| BCC     | - | Behavioral Change Campaign              |
| CDD     | - | Community Drug Distributor              |
| ID      | - | Identification number                   |
| DOT     | - | Directly Observed Therapy               |
| SAM     | - | Severe Acute Malnutrition               |
| HIV     | - | Human Immunodeficiency Virus            |
| EA      | - | Enumeration Area                        |
| FGD     | - | Focus Group Discussion                  |
| RDT     | - | Rapid Diagnostic Test                   |
| DHOs    | - | District Health Officials               |
| SP      | - | Sulfadoxine-pyrimethamine               |
| AQ      | - | Amodiaquine                             |
| HIV     | - | Human Immunodeficiency Virus            |
| ARF     | - | Adverse Reaction Form                   |
| IRB     | - | Institutional Review Board              |

# 1 Introduction

In 2010, malaria claimed an estimated 660,000 lives globally, with 90% of these deaths occurring among children under-five and pregnant women. Nigeria alone represents more than one-quarter of all global malaria deaths and has a population of over 9 million children under-five years of age in the northern States. Malnutrition is the number one risk factor for under-five child deaths and is an underlying factor in the death of an approximately 400,000 children in Nigeria each year. Previous studies suggest there is an association between malaria and nutrition. Nearly 50% of all malaria deaths are attributable to malnutrition. Investment in malaria interventions has been shown to significantly increase mean weight-for-age and mid-upper arm circumference scores which are both recognized nutrition indicators. Furthermore, malnutrition can increase the severity of malaria. Nigeria has the highest prevalence of malnourished children in all of Africa, with nearly 9% of children under the age of five (approximately 2.4 million) suffering from severe acute malnutrition (SAM). In several of Nigeria's northern states, the levels of acute malnutrition exceed the WHO "emergency" threshold of 15%.

Nigeria's northern State of Kano, has a population of nearly 2.5 million children under-five and an under-five mortality rate of 217 per 1,000. Twenty-five percent of all under-five deaths in Kano (approximately 132,000 annually) are attributable to malaria. To address this burden, in 2013, the Clinton Health Access Initiative (CHAI) in collaboration with the Kano State Ministry of Health (KSMOH) in Northern Nigeria piloted the delivery of Seasonal Malaria Chemoprevention (SMC) as an approach to reduce the burden of malaria. SMC was endorsed by the World Health Organization (WHO) in March 2012 and is defined as the intermittent administration of a full treatment course of antimalarial medication to children living in areas of highly seasonal transmission. The purpose of SMC is to prevent malaria by maintaining therapeutic antimalarial drug concentrations in the bloodstream throughout the period of greatest malarial risk. The WHO recommends SMC for children under-five years living in the Sahel sub-region of Africa during the period known as the "long rains." One recommended antimalarial dosing structure for SMC is four treatment courses of sulfadoxine-pyrimethamine + amodiaquine (SP-AQ), offered as a three day dosing regimen, taken once per month for four consecutive months over the

---

 *World Malaria Report 2012*. Geneva: World Health Organization, 2012. Internet resource.

 Calculated by applying the 45% of all child deaths attributable to malnutrition to the 3.24 million child deaths in sub-Saharan Africa reported in the Levels & Trends in Child Mortality Report from UNICEF, WHO, the World Bank, and the UN in 2013.

 The Lancet. Maternal and Child Undernutrition: Global and Regional Exposures and Health Consequences. January, 2008.

In Kano State where CHAI has historically assisted the Kano State Malaria Control Program (KSMCP) with SMC delivery, malaria is highly seasonal and spikes during the rainy season, typically during the two to four month period beginning in July/August of each year when SMC is recommended. The rainy season coincides with the “hunger season”, typically starting one month after the rains have begun. During these months children are extremely vulnerable to dying of causes that are completely preventable. One recommended treatment for malnutrition is Lipid-based Nutritional Supplements (LNS). Plumpy’DozTM is LNS designed for the treatment of moderate acute malnutrition and the prevention of undernutrition. Plumpy’DozTM is designed to sustain the growth of young children, improve their motor and cognitive development, and reduce the incidence of malnutrition—whether acute or chronic—during critical periods of food and nutrition insecurity. As they can be given without a medical prescription, LNS are often used in association with blanket feeding programs targeting young children who are not malnourished but who are at risk of malnutrition.

CHAI’s 2013 SMC pilot demonstrated that SMC coverage was optimized through door-to-door delivery of SP-AQ where nearly 90% of eligible children received at least one treatment course of SMC during the intervention period. As the 2014 SMC campaign will rely on the door-to-door delivery method, using the 2014 SMC campaign to deliver LNS could be one avenue for reaching children at-risk for both malaria and malnutrition at a critical time for both health concerns; however, to date this has never been done. Beyond reductions in malaria and malnutrition, packaging LNS with the SMC campaign may serve as an added incentive for parents/guardians to accept SMC preventative treatment, adhere to dosing guidelines, and incentivize caregivers to stay at home during regularly scheduled delivery periods resulting higher SMC coverage. CHAI, in collaboration with the KSMOH, will test SMC and LNS coverage, malaria, and malnutrition outcomes reached by packaging the delivery of LNS through the door-to-door SMC campaign.

## 2 Research Goal, Objectives, and Significance

The primary goal of this study is **to compare the intervention coverage and health outcomes achieved among children 6-24 months by packaging the delivery of LNS through the SMC campaign as compared to the delivery of SMC alone.** This goal will be guided by three research questions presented in Table 1.

Table 1: Research questions.

---

 Sahelian sub-regions recommended for SMC are those with a clinical attack rate greater than 0.1 per transmission season in the target age group, or areas with >10 of 100 under-fives experiencing clinical malaria during the rainy season.

 WHO Global Malaria Programme (March 2012). *WHO Policy Recommendation: Seasonal Malaria Chemoprevention (SMC) for Plasmodium falciparum malaria control in highly seasonal transmission areas of the Sahel sub-region in Africa.*

| #   | Research Questions                                                                                                                                                                                                           | Methodology                                                                                                                 |
|-----|------------------------------------------------------------------------------------------------------------------------------------------------------------------------------------------------------------------------------|-----------------------------------------------------------------------------------------------------------------------------|
| Q-1 | Does packaging the delivery of LNS through the SMC campaign result in higher SMC coverage and adherence within target communities among children 6 to 24 months, compared to delivery of SMC alone?                          | Cross-sectional household survey (midline)                                                                                  |
| Q-2 | Does packaging the delivery of LNS through SMC campaigns result in reduced malnutrition outcomes (stunting, wasting, and underweight) among children 6 to 24 months, compared to SMC alone?                                  | Repeated cross-sectional household surveys (baseline, midline, and endline 6 months after the final round of interventions) |
| Q-3 | Does treatment with SMC or the packaging of LNS through the SMC campaigns change the odds that a child is diagnosed with clinical malaria cases including severe cases among children 6 to 24 months, compared to SMC alone? | Malaria Case Tracker (case-control study)                                                                                   |

The findings from this study will allow the Ministry of Health and State Malaria Control Programs in the nine eligible States for SMC in Nigeria to make a decision regarding whether LNS should be delivered through the SMC door-to-door campaigns in at risk settings in order to achieve high coverage rates and improve health outcomes. Additionally, the results will help inform global policy makers and implementers regarding the co-packaging of SMC and nutrition interventions.

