### 3 Hypotheses and Success Metrics

The primary hypotheses that will be tested in this study as well as the endpoint indicators for success are listed in Tables 2 and 3 below and are based on three primary outcomes: coverage, reduction in malnutrition, and reduction in clinical malaria.

Table 2: Research Hypotheses

| #   | Hypotheses                                                                                                                                                |
|-----|-----------------------------------------------------------------------------------------------------------------------------------------------------------|
| H-1 | Coverage and adherence of SMC among eligible children in areas where SMC + LNS was delivered will not differ from areas where only SMC was delivered.     |
| H-2 | Nutrition indicators among eligible children in areas where SMC + LNS was delivered will not differ from areas where only SMC was delivered.              |
| H-3 | The odds of being diagnosed with clinical malaria cases including severe cases among eligible children who received SMC + LNS, SMC, or neither treatment. |

Table 3: Performance Metrics

| Hypotheses | Performance Indicator | Indicator Definition and Unit of Measurement                                                                                                                                                                                                                                                                                                                                                                                                                    | Data Source                                    |
|------------|-----------------------|-----------------------------------------------------------------------------------------------------------------------------------------------------------------------------------------------------------------------------------------------------------------------------------------------------------------------------------------------------------------------------------------------------------------------------------------------------------------|------------------------------------------------|

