## 4 Intervention Design

### Study Site and Population

Table 4: Overview of the study population for each treatment type.

| Intervention Arm                                               | LGA    |
|----------------------------------------------------------------|--------|
| Arm 1: SMC (Children 3-59 months)                              | Madobi |
| Arm 2: SMC (Children 3-59 months) + LNS (Children 6-24 months) | Madobi |

This study has two intervention arms: SMC delivery and SMC + LNS delivery. Of note, SMC is specified by the WHO for children 3-59 months and Plumpy'doz' is specified by UNICEF and WFP for children 6-24 months, this study will treat children in intervention arms based on these recommendations (see Table 4: Intervention Arm). In the Local Government Area (LGA), Madobi, between 1 and 3 wards were selected for each intervention arm. An overview of the study population for each intervention area is presented in Table 4. The intervention areas were chosen to be as similar as possible in terms of pre-determined criteria that included malaria incidence reported at public health centers, wasting prevalence, malaria endemicity, socio-economic status, urbanicity, mobility and cultural identity of the population, density of health facilities, presence of a CMAM facility, and population demographic structures (dependency ratio, fertility rate and household size, infant mortality, and birth spacing).

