### **Phase 2: Intervention Administration**

Phase 2 will make use of the existing network of Community Drug Dispensers (CDDs) that work on other health campaigns in Kano. Community lists will be obtained for each ward from the Village head or the CDD LGA Focal person. Within each ward, CHAI study staff will visit each identified community and a household sampling frame will be obtained from each community headman. In the event that a Village head cannot produce an accurate listing or new communities have developed that are not present on the village head's list, the village headman and CDDs will be used to create a census of their community. CDDs alongside study staff will visit each household on the sampling frame and obtain accurate listings of homes with at least one child under-five residing within it in the treatment area. Supplementary data will also be collected from parents/guardians including data on the number of children 3-59 months of age residing in each home, child and parent's/guardian's names, and contact details (e.g. phone number of parent/guardian, address of home).

CHAI will train pre-existing CDDs on the proper administration of SP-AQ/*Plumpy doz'* in a 1-day training course. During each administration period, each CDD will be assigned to 100 households that they will cover over the course of one week. The CDDs will visit children and their parents/guardians in their homes four times on a monthly basis (July-October) and deliver the treatment. After each visit, CDDs will instruct parents/guardians that they will return four weeks later, on the *same day of the week* as the first SMC visit to deliver the next treatment.

All treatments provided will be recorded in two places: a treatment card that is left with the parent/guardian of the child and the CDDs administration register. Each child will be assigned a unique Identification number (ID) and the treatment card and the child's name in the CDDs administration register will be labeled with the unique ID. The treatment card will be filled out by the CDD at first contact, and given to the parent/guardian of each child. Information collected on the treatment card will include the child's name, birthday, dose of SP-AQ and amount of LNS provided, date of

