## 5 Monitoring and Evaluation Methods

Table 7 presents the data collection methods used for evaluation of the performance metrics previously outlined in Table 3, and the target population. Estimating intervention treatment coverage will be assessed through the midline cross-sectional household survey. The impact of interventions on nutrition health outcomes will be assessed through the three repeated cross-sectional household surveys. The impact of interventions on malaria health outcomes will be assessed through a case-control study using a malaria tracker where cases will be recruited from health facilities and control from the midline household survey. Cases will be recruited from facilities due to the challenge of identifying sufficient numbers of acute malaria episodes via monthly household surveys. Focus Group Discussions (FGDs) will be used to provide context to the results. CHAI will contract a private data collection firm to carry out the household surveys, case control study, collection of health facility records, and completion of FGDs. CHAI will carry out the data analysis and provide CIFF the full clean datasets from the firm upon request to validate findings.

Table 7: The data collection methods used for evaluation of the performance metrics previously outlined in Table 3, and the target population.

| Data Collection Method                                              | Timeline      | Inclusion Age*                | Location                     | Indicators                         |
|---------------------------------------------------------------------|---------------|-------------------------------|------------------------------|------------------------------------|
| Baseline Household Survey                                           | July 2014     | 6-24 months                   | Community                    | Malnutrition                       |
| Midline Household Survey
Nutrition Module
SMC Coverage Module | November 2014 | 6-28 months
(3-63 months)^ | Community                    | Malnutrition
Treatment Coverage |
| Endline Household Survey                                            | May 2015      | 12-34 months                  | Community                    | Malnutrition
Prevalence         |
| Malaria Case Tracker                                                | Continuous    | 6-24 months in July 2014      | Health Facility
Community | Malaria Incidence                  |

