## **Evaluation Data Collection Procedures and Participant Recruitment**

### **Household Surveys**

In total, three household surveys will be conducted, a baseline in July of 2014 alongside the first administration, midline in November 2014 after Round 4 of administration, and a final survey in May 2015, six months post intervention. The baseline survey will provide baseline information on demographics, and nutrition indicators. The midline survey will provide an estimate of the intervention coverage and adherence to SMC in addition to the nutrition indicators. The final survey six months after the endline administration will determine if there is a long-term health impact in terms of the nutrition indicators. Each questionnaire will be a pre-tested, interviewer-administered questionnaire lasting about 45-60 minutes.

For each survey, 1,500 households with at least one child that meets the inclusion age outlined in Table 6 will be selected to participate in the survey (a minimum of 750 households in each intervention study arm: SMC and SMC + LNS). This sample size is powered to measure a 10% difference in the outcome indicator (intervention coverage or nutrition indicator is estimated at 50%, which is conservative and gives the largest sample size) between the two intervention areas with an alpha of 5% and a power of 90%, and a design effect of 1.5.

A multistage stratified sampling strategy will be used for household selection. The sampling frame for the survey will come from the national sampling frame, which lists all the Enumeration Area (EA) maps of the 2006 Population and Housing Census conducted by the National Population Commission. Assuming 25 households are interviewed per EA, EAs are needed to achieve the total target sample size – in other words 30 EAs in each intervention arm. To account for the unlikely event that a randomly chosen EA did not contain 25 eligible households, 20 additional EAs will be randomly selected per intervention arm, making a total of 100 EAs selected per survey round (50 EAs per intervention arm). The supplemental EAs will only be used if needed. Using the 2013 population projections of each ward, we will use a probability-proportional-to-size methodology to select an appropriate number of EAs within each ward.

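### H-1 rests on one post-delivery coverage survey in purposively chosen areas with no earlier uptake measure, so an existing acceptance gap could mimic or mask an LNS incentive effect

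*Protocol*

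**What the plan says.** Coverage is the first of the three primary outcomes in section 3. H-1 is a contrast between areas: "Coverage and adherence of SMC among eligible children in areas where SMC + LNS was delivered will not differ from areas where only SMC was delivered".

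Table 1 gives the data source for Q-1 as "Cross-sectional household survey (midline", and Table 3 names the midline survey for both coverage and adherence. Section 5 repeats it: "Estimating intervention treatment coverage will be assessed through the midline cross-sectional household survey". Under Household Surveys the timing is "midline in November 2014 after Round 4 of administration".

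A July survey is fielded in both arms, but its described content is narrower: "The baseline survey will provide baseline information on demographics, and nutrition indicators". Table 7 lists malnutrition as its only indicator. Q-2, by contrast, has baseline, midline and endline surveys.

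On how the arms were formed, Study Site and Population says "between 1 and 3 wards were selected for each intervention arm", all in one LGA, and "The intervention areas were chosen to be as similar as possible in terms of pre-determined criteria". No random allocation is stated. The listed criteria cover malaria, wasting, socio-economic status, urbanicity, mobility, cultural identity, health facilities and demography. Neither earlier SMC coverage nor uptake of any other campaign is among them.

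**The concern.** H-1 is meant to show whether LNS acts as an incentive to accept SMC, the mechanism proposed in the Introduction. The result is intended to inform nine States. A single difference measured after delivery, between a few chosen areas, contains two things: any effect of LNS, and any difference in acceptance or distributor performance that was there already. The nutrition question has a starting value against which such a difference would show; the coverage question has none.

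This cannot be left to an analysis plan. Adjustment needs data on earlier uptake, and the protocol's description of the July survey does not provide for collecting them.

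**Working it through.** **1. Is there any measure of uptake before LNS?**

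| Source | Starts | Measures uptake before LNS? |
|---|---|---|
| July survey | July 2014 | No: demographics and nutrition |
| Monthly coverage indicator (Table 3) | Round 1, asked at midline | No: LNS is given from round 1 |
| Treatment cards and registers | Round 1 | No, for the same reason |
| 2013 pilot figure (nearly 90%) | 2013 | Not given by ward or arm, nor tied to the study wards |
| Midline coverage in older children | November 2014 | No, but these children receive SMC without LNS |

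**2. The plan's own sample size.** Inputs from Household Surveys: 50% against 60%, alpha 5% (two-sided assumed), power 90%, design effect 1.5, 750 households per arm.

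- Unpooled formula: n = (1.96 + 1.2816)² × (0.25 + 0.24) / 0.10² = 514.9 per arm. Times 1.5 gives 772, within 3% of 750.
- Power with 750 / 1.5 = 500 effective per arm: 0.89.

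The stated figure is consistent with its inputs. The issue is what the contrast estimates, not its precision.

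**3. Effect of an existing gap when LNS does nothing.** One child per household is assumed, so there are 500 effective children per arm.

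At an assumed coverage p, SE = √(2p(1−p)/500), and P(significant) = P(|Z + gap/SE| > 1.96).

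- p = 75%: SE = √(2 × 0.75 × 0.25 / 500) = 2.74 points
- p = 50%: SE = √(2 × 0.25 / 500) = 3.16 points

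| Assumed gap | Coverage 75% | Coverage 50% |
|---|---|---|
| 3 points | 19% | 16% |
| 5 points | 45% | 35% |
| 8 points | 83% | 72% |

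The nominal rate is 5%. An existing 10-point gap at 50% coverage would be declared significant 89% of the time, the same as a true 10-point effect. More households per arm would not help, because the gap does not shrink with sample size.

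**4. How far could a baseline proxy correct this?** Suppose true ward coverage varies with SD σ = 5 points, there are w = 2 wards per arm, and the proxy correlates ρ with SMC uptake. The SD of the difference is √(SE² + 2σ²(1−ρ²)/w), and the false-positive rate is P(|Z| > 1.96 × SE / SD). With SE = 2.74 (SE² = 7.5):

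| ρ | SD of difference (points) | False-positive rate |
|---|---|---|
| 0 (no proxy) | √(7.5 + 25) = 5.70 | 35% |
| 0.5 | √(7.5 + 18.75) = 5.12 | 29% |
| 0.8 | √(7.5 + 9) = 4.06 | 19% |
| 0.9 | √(7.5 + 4.75) = 3.50 | 13% |

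With σ = 2 and no proxy, the SD is √(7.5 + 4) = 3.39 and the rate is 11%. These figures treat the adjustment slope as known, which flatters the correction. The inflation itself also reflects the small number of wards, not only the missing baseline.

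**The case against.** Several points on the other side stand.

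- **Something collected does bear on it.** A reader might infer that no planned data could reveal a prior gap. That goes too far: the note to Table 7 has midline SMC coverage recorded for all children 3-59 months in the home. Those too old for LNS receive SMC alone in both arms, so a similar arm gap in them would be a warning. The check is partial, because they share a home with an LNS-age child and the incentive may reach them. The protocol does not use them for H-1.
- **The matching is not blind to acceptance.** Mobility and cultural identity are on the list, the list is introduced as what the criteria included, and CDD training and workload are the same in both arms. This may shrink a gap; it neither measures nor removes it.
- **Pilot history is unknown.** A reader might infer that the arms differed in exposure to the 2013 pilot. The protocol does not say where in the State the pilot ran or whether any study ward took part.
- **Adjustment is weak.** With one ward per arm, ward uptake is indistinguishable from arm. Enumeration areas are selected for each survey round, so July and November areas need not coincide. Receipt of another campaign is only a proxy, and it says nothing about home dosing on days 2 and 3.
- **The questionnaire is not shown.** Its content is known only from the summary and Table 7. Both leave coverage out of July and include it at midline.

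**Conclusion.** The point holds as a limit on what H-1 can conclude. As written, the November contrast cannot separate an LNS incentive from an existing difference between the chosen areas.

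A reader might infer that a gap would necessarily be reported as a benefit of LNS. The documents do not support that: its direction is unknown, and a gap favouring the SMC-only area would hide a real effect. Nor do they show that a gap exists.

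The probabilities in steps 3 and 4 rest on assumed gaps, ward variation and correlations, and on a 75% coverage that lies between the protocol's planning value of 50% and the pilot's figure of nearly 90%. They show that gaps smaller than the 10 points the survey was sized for would often produce a significant result. They are not estimates of bias in this study.

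**What to change.** 1. **July questionnaire, both arms.** Add one or two items per listed child: receipt of the most recent door-to-door campaign round, checked against a card where one exists, and SMC in 2013 for children old enough. The CDDs are described as workers "that work on other health campaigns in Kano", so an earlier round should be available to ask about. Because the July survey runs alongside the first administration, the items must refer to a round before it. If the 2013 rounds also ended in October (not stated), a child would need to be about 9 + 3 = 12 months old in July 2014 to have qualified. Report the July gap by arm beside the November gap, and treat any adjusted estimate as a sensitivity analysis.
2. **Older children at midline.** Report the arm gap in SMC coverage among children too old for LNS beside the gap in LNS-age children, noting possible spill-over within the household.
3. **Pilot history and wording.** State whether the wards in each arm took part in the 2013 pilot; re-selecting wards already chosen is not needed for this. Word the H-1 conclusion as a difference between areas unless these checks show no prior gap.

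The cost is a minute or two in a 45-60 minute interview already fielded in both arms, plus two extra reported comparisons. The correction is partial, and the new items do not address the adherence component of H-1.
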